Investigating LIFUP in Anhedonic Depression (ILIAD) is a complementary interventional study to a broader observational study: Operationalizing Digital PhenoTyping in the Measurement of Anhedonia (OPTIMA). These two studies are distinct and have only partially overlapping subject populations; while OPTIMA recruits participants across the spectrum of anhedonia severity, ILIAD only enrolls participants with high levels of anhedonia. Additionally, ILIAD recruits from both the OPTIMA subject pool and from external sources. However, many elements of the two studies are harmonized in order to facilitate potential merging of data. Both of these studies are performed in the Wellcome Leap Multi-Channel Psych Consortium, a broader multi-site program that seeks to develop integrated models of anhedonic depression.^1^

This sham-controlled, double-blinded study investigates the impact of multiple sessions of LIFUP targeting either the left caudate head or right nucleus accumbens on an array of anhedonia-related self-report and neuroimaging measures. The two targets for this study were selected due to the literature implicating them in the pathophysiology of anhedonic depression and their central role in mesolimbic reward circuitry (Haber and Knutson, 2010; Wang et al., 2021). Reduced caudate volume has been found to correlate with anhedonia severity, and both the nucleus accumbens and the caudate have been found to have significantly weaker reward responses in individuals with major depressive disorder when compared to healthy controls (Pizzagalli et al., 2009). The left caudate in particular was selected for this study due to literature suggesting that a longitudinal increase in left caudate connectivity with the bilateral superior frontal gyrus may correlate with anhedonia improvement over the same time period (Yang et al., 2022). The right nucleus accumbens was chosen based on literature showing a correlation between anhedonia severity and altered right nucleus accumbens connectivity (Liu et al., 2021). However, the right nucleus accumbens was removed from this study midway through due to funding changes.

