The initial design of this study utilized three gel pads, one of which was sham. Participants in both the nucleus accumbens and caudate group were randomized to gel pads A, B, and C at equal rates, such that 1/3 of participants would receive active caudate, 1/3 would receive active nucleus accumbens, 1/6 would receive sham caudate, and 1/6 would receive sham nucleus accumbens. When it was determined due to funding changes that the study design should be reduced to two conditions, one individual on the team was unblinded by steering committee consensus. This individual then performed analyses on the imaging data from the Card Guessing Task to determine changes in reward attainment and anticipation across LIFUP in each group in order to guide a data-informed decision on which condition to keep in the study. Results of the analyses were then presented to the investigative team, keeping conditions concealed. Based on these results, investigators chose a condition to keep in the revised protocol, and an alternate condition was designated to keep in the case that the primary choice was sham. Investigators were informed that the nucleus accumbens target would be removed, but were not informed which group in the presented analyses was the active caudate group. The only individuals who were knowledgeable about condition assignment were the individual who performed the analysis and the research program manager who supervised the staff performing LIFUP. Conditions remained concealed to all other members of the research team. A total of six participants received active nucleus accumbens LIFUP prior to the removal of this condition.

To maximize the integrity of blinding, outcome assessors refrain from making any guesses regarding active/sham conditions. In the case where a participant guesses their condition based on how they feel during sessions, staff listen to their thoughts but refrain from discussion, and no records of these guesses are kept.

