### 4.2 Analysis of MRI data

Primary imaging analyses will include pre vs. post-LIFUP analysis of reward processing, activation, and connectivity of the caudate and nucleus accumbens as measured with resting state fMRI and task fMRI. Preprocessing of functional MRI data will be done with fMRIprep, Tedana, and XCP-D (Esteban et al., 2020; DuPre et al., 2021; Mehta et al., 2023). Resting state and task fMRI analyses will be conducted using the fMRIB Software Library (FSL) (Woolrich et al., 2001, 2004).

The functional MRI data collected during the Card Guessing Task will be used to assess changes in reward processing across active and sham LIFUP. Reward processing will be assessed by comparing fMRI activation during gain vs. loss trials as well as during gain trials vs. inter-trial intervals. Then, a repeated-measures ANOVA design will be used to assess the effect of time and group on these lower-level contrasts. We hypothesize that participants who received active LIFUP will have higher reward-responsive activity in their respective target regions (i.e., either nucleus accumbens or caudate) compared to those who received sham. This would represent a normalization of activity, as decreased activity has been observed in both regions in response to reward-related tasks (Wang et al., 2021).

Connectivity values between multiple regions of interest will be extracted from the resting state fMRI data in order to investigate changes across LIFUP vs. sham using multi-level modeling. Some particular variables of interest for this analysis due to prior implications for anhedonia in the literature include default mode network average connectivity, left caudate to superior frontal gyrus connectivity, right nucleus accumbens shell to left subgenual anterior cingulate cortex, and right nucleus accumbens core to right precuneus (Dunlop et al., 2019; Liu et al., 2021; Yang et al., 2022).

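### The retained target was chosen on Card Guessing Task results and the same task data are tested again without allowance for that choice, which modestly biases caudate versus sham towards benefit

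*Protocol article*

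**What the plan says.** Section 3.1.3 of the protocol article describes the redesign. Funding forced a reduction to two conditions, and "one individual on the team was unblinded by steering committee consensus". That person "performed analyses on the imaging data from the Card Guessing Task to determine changes in reward attainment and anticipation across LIFUP in each group". Then: "Results of the analyses were then presented to the investigative team, keeping conditions concealed". The choice followed from what was shown: "Based on these results, investigators chose a condition to keep in the revised protocol". A fallback was also named, for use if the group picked first turned out to be the sham group. On the size of the dropped arm: "A total of six participants received active nucleus accumbens LIFUP prior to the removal of this condition".

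Section 3.3.3.2 names anticipation and attainment as the task's main neural outcomes, which are the quantities used for the choice. Section 4.2 counts reward processing on task fMRI among the primary imaging analyses and says: "The functional MRI data collected during the Card Guessing Task will be used to assess changes in reward processing across active and sham LIFUP". The group-level test is a repeated-measures ANOVA on time and group, with a directional hypothesis of higher reward response in the stimulated target than under sham. It does not separate participants enrolled before the redesign from those enrolled after it, and it mentions no allowance for the choice of target.

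The Introduction gives the reason for the change as "the right nucleus accumbens was removed from this study midway through due to funding changes". Sections 3.1.1 and 5 likewise give budget as the reason.

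**The concern.** Funding explains why an arm had to go; the task data decided which one. The alternate rule means that sham could not be the condition retained, so the step amounts to choosing between two active targets on a measure that is later a primary imaging outcome. An arm kept because its early results looked good carries its early random high into the final average. The sham arm carries no matching excess. The caudate-versus-sham difference on this task is then too large on average, and its p-value too small on the side that would be read as success. At stake is the credibility of one primary imaging result in a small trial.

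**Working it through.** The article gives no alpha, SD, effect size or power for this outcome, so there is no stated figure to reproduce.

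**Inputs**
- Dropped arm at selection: 6 (Section 3.1.3). The original allocation was one third to each active target and one third to sham, so about 6 per group is assumed, with 4 to 8 as the range.
- Final size: at least 40 evaluable (Section 2.1). Removing the 6 accumbens participants and splitting equally gives (40 − 6)/2 = 17 per arm. The enrolment ceiling of 100 gives (100 − 6)/2 = 47.
- Assumed: no true effect, SD of the change score = 1, two-sided 5% level, the better-looking target kept, and one outcome common to both targets.

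**Bias.** Let n1 be the group size at selection and n the final arm size.
- The larger of two independent null means exceeds zero on average by (1/√π) × 1/√n1 = 0.564/2.449 = 0.23 SD.
- Stage 1 makes up n1/n = 6/17 = 0.353 of the final caudate mean, so the final bias is 0.23 × 0.353 = 0.081 SD.
- The standard error of the difference is √(2/17) = 0.343 SD, so the bias is 0.081/0.343 = 0.24 standard errors.

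**Error rates.** The correlation between the final standardised difference and the selection contrast is ρ = ½√(n1/n) = ½√(6/17) = 0.297. The benefit-side error is 2 × P(Z > critical value and selection contrast > 0). By symmetry the harm side falls by exactly as much as the benefit side rises, so the two-sided rate does not change. Using the t critical value:

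| n1 | n per arm | ρ | Bias (SD) | Benefit-side error | Harm-side error |
|---|---|---|---|---|---|
| 4 | 17 | 0.243 | 0.07 | 3.6% | 1.4% |
| 6 | 17 | 0.297 | 0.08 | 3.8% | 1.2% |
| 8 | 17 | 0.343 | 0.09 | 4.0% | 1.0% |
| 6 | 47 | 0.179 | 0.03 | 3.3% | 1.7% |

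Simulation with 400,000 trials per scenario agrees (6 and 17: bias 0.082 SD, benefit 3.8%, two-sided 5.0%). If each target was instead judged in its own region against sham, the 6-and-17 case gives 0.11 SD and 4.3%.

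**Pooled contrast.** Selection depends on the caudate mean minus the accumbens mean. With equal stage-1 sizes, that difference is uncorrelated with their sum, and pooling keeps the sum. Simulation gives bias 0.00 SD and benefit-side error 2.5%.

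**Remedies.** These were checked at 6 and 17, with SD treated as known, conditional on caudate being kept (1,000,000 simulated trials). The combination test is inverse-normal with weights √(6/17) and √(11/17), and a closed test with a Dunnett-adjusted stage-1 p-value.

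| Analysis | Benefit-side error, no effect | Power, assumed caudate effect 0.8 SD, accumbens none |
|---|---|---|
| All data, unadjusted | 3.8% | 66% |
| Stagewise combination | 2.5% | 59% |
| Post-redesign only (11 per arm) | 2.5% | 47% |

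**The case against.** Several points on the other side are sound.

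- **Which contrast.** Section 4.2 speaks of active and sham stimulation and of each group's own target region, so the accumbens participants may stay in. A pooled comparison would be unbiased. That stands as a limit: the bias belongs to caudate versus sham. It does not dispose of the point, because pooling is stated only for self-report (Section 4.1), where a caudate-only comparison is also planned, and the imaging hypothesis is target-specific.
- **Direction.** No selection rule is given, and two variables were looked at. Keeping the better-looking target is the natural reading of a choice guided by results with a fallback against sham, but it is an inference. If the choice rested on a measure only correlated with the tested contrast, the bias shrinks in proportion to that correlation.
- **Masking.** A reader might infer that the investigators knew the arms when they chose. They did not; they saw concealed labels. Masking guards against preference for a label, not against selecting a random high.
- **Unseen analysis plan.** It may hold an adjustment. The article nevertheless names an ordinary test on the very outcome used for selection, so the point rests on what is stated.
- **Disclosure.** A reader might infer that the funding explanation hides a data-driven choice. The documents do not support that: funding did cause the reduction, and Section 3.1.3 openly describes how the arm was picked. The shorter accounts elsewhere are incomplete, not contradictory.

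**Conclusion.** The point holds for the caudate-versus-sham contrast on the Card Guessing Task, at modest size: a bias of roughly a quarter of a standard error at the minimum sample, with the false-positive risk tilted towards benefit and not raised in total. It rests on the better-looking target having been kept, about 6 per group at selection, and equal arms afterwards. It weakens as the final sample grows.

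A reader might infer that the primary results as a whole are compromised. The documents do not support that. No effect on the PHQ-14, PVSS, EMA, spectroscopy or resting-state results has been shown, and the pooled active comparison is essentially unbiased. The plan should be changed, but the flaw does not invalidate the trial.

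**What to change.** In Section 4.2, before final unblinding:

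- State that the caudate-versus-sham Card Guessing Task contrast is analysed by stage. Combine participants from before and after the redesign with an inverse-normal test whose stage-1 p-value is adjusted for choosing between two targets, and fix the weights from the actual stage sizes.
- Report the post-redesign-only estimate beside it.
- Label the unadjusted all-data caudate-versus-sham result as selection-affected and exploratory.
- Describe the test as fixed before final analysis, not as prespecified from the start, because stage-1 group results have already been seen.

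The cost is one extra analysis and some power: about 7 percentage points in the example above, part of which is only the inflation being removed. Making the post-redesign participants the sole confirmatory set also removes the bias, but it gives up 6 of 17 per arm and about 19 points of power in the same example, so it serves better as the accompanying estimate.

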### 3.2 Self-report assessments

#### 3.2.1 Primary outcome assessments

The primary self-report outcome measures for this study are the Patient Health Questionnaire (PHQ-14), the Positive Valence Systems Scale (PVSS-21), and the Ecological Momentary Assessment (EMA). The PHQ-14 and PVSS-21 are completed weekly throughout the course of study participation; the schedule of EMA administration is described below and in Figure 1.

##### 3.2.1.1 Patient Health Questionnaire - 14 item version (PHQ-14)

The PHQ-14 is a modified version of the Patient Health Questionnaire (Kroenke et al., 2010) developed by Cohen, Cohen & Fried (in preparation)^2^ that separates the four compound symptoms from the original PHQ into individual items (e.g., “poor appetite or overeating” was split into two items) and adds two new symptoms: irritability and libido. Score is summarized as a total score aligned with the PHQ-8, where a higher score indicates the severity of depressive symptoms; further information and a copy of the full inventory are available in the Supplementary Method S4 and Supplementary Forms. This assessment was chosen as a primary outcome measure in order to provide information about any changes in overall depressive symptoms in response to LIFUP, given the association between depression symptoms and the LIFUP target regions.

##### 3.2.1.2 Positive Valence Systems Scale (PVSS-21)

The PVSS-21 (Khazanov et al., 2020) is a 21-item self-report survey assessing features of reward processing associated with anhedonia. This assessment was selected as a primary outcome measure due to the literature demonstrating connections between alterations in caudate and nucleus accumbens activity and anhedonia symptoms (Wang et al., 2021).

##### 3.2.1.3 Ecological Momentary Assessment (EMA)

The EMA is a 3-part, 19-item assessment that measures current mood and experiences.^3^ Part 1 contains 8 questions about current mood, e.g. “How sad are you feeling right now?” Part 2 asks participants to rate their agreement with 6 reward-related statements, such as “I'm looking forward to an upcoming activity”. Part 3 asks participants to rate their enjoyment of their current company and activities on a 7-point likert scale. This assessment was selected as a primary outcome measure due to its ability to provide data on immediate mood and reward-related states with high temporal resolution, thereby minimizing the impact of recall biases that have been documented for surveys asking about depressive symptoms over a longer time range (Horwitz et al., 2023).

For non-OPTIMA participants, baseline EMA data is collected 5 × a day for the 15 days prior to the first LIFUP session; for OPTIMA participants, baseline data is taken from the 5 × daily EMAs collected at several points during the OPTIMA protocol. All participants subsequently complete 1 × daily EMA from the day of LIFUP 1 through the day of LIFUP 3, and 8 days of 5 × daily EMAs starting 7 days prior to scan 2 through the day of scan. If scan 2 is < 8 days after LIFUP 3, the 5 × daily EMAs will override the 1 × daily EMAs on any overlapping days. Lastly, an additional 8 days of 5 × daily EMA data is collected during Week 5 of the protocol. See Figure 1 for an illustration of the EMA timeline. Further information regarding the development of this assessment and a copy of the full assessment are available in the Supplementary Method S1 and Supplementary Forms.

#### 3.2.2 Secondary outcome measures

An additional set of behavioral questionnaires assessing aspects of anhedonia, depression, anxiety, and general mental wellbeing are collected at baseline and at the end of the study. A list of assessments used for this study is available in Table 2, alongside descriptions of each assessment. Two secondary outcome assessments, The Modified SITBI-R + CSSRS-SR (MSC-SR)^4^ and the Eudaimonic Wellbeing Questionnaire,^5^ were developed by the study team for the purposes of this study; further information regarding the development of these assessments is available in the Supplementary Methods S2, S3. The schedule of administration for these measures is available in Supplementary Table S2, and full assessments are available in the Supplementary Forms.

**Table 2 T2:** A list of the self-report questionnaires, neurocognitive tests, and interviews administered as part of the ILIAD protocol and descriptions of each measure.

**Assessment**	**Assessment type**	**Description**
Ecological Momentary Assessment (EMA)	Primary outcome	Self-reported current mood, environment, experiences, and anhedonic state
Positive Valence Systems Scale (PVSS-21)	Primary outcome	Self-reported index of anhedonia and reward processing, 21 items
Patient Health Questionnaire - modified (PHQ-14)	Primary outcome	Self-reported depression severity, 14 items
Patient Health Questionnaire (PHQ-9)	Secondary outcome/adverse event monitoring	Self-reported depression severity, 9 items
Quick Inventory of Depressive Symptoms (QIDS-SR15)	Secondary outcome	Self-reported depression symptoms, 15-items
Brief Irritability Test (BITe)	Secondary outcome	Self-report irritability measure, 5-items
Modified SITBI-R+CSSRS-SR (MSC-SR)	Secondary outcome	Self-report of suicidal ideation and behavior
Generalized Anxiety Disorder Questionnaire (GAD-7)	Secondary Outcome	Self-reported anxiety symptoms, 7-items
Work and Social Adjustment Scale (WSAS)	Secondary outcome	Self-reported functional impairment of current symptoms in work/school, social life, and family life
World Health Organization (WHO)-5 Wellbeing Index	Secondary outcome	Self-reported current mental wellbeing
Pittsburgh Sleep Quality Index (PSQI)	Secondary outcome	Self-reported recent sleep quality
Snaith-Hamilton Pleasure Scale (SHAPS)	Secondary outcome	Self-reported hedonic experience or positive valence
Apathy Motivation Index (AMI)	Secondary outcome	Self-report index of apathy and motivation
Ruminative Response Scale (RRS) brooding subscale (state)	Secondary outcome	Self-reported symptoms of rumination
Eudaimonic Wellbeing Questionnaire (EWBQ)	Secondary outcome	Self-reported wellbeing focused on values, meaning and purpose in life.
Treatment History Questionnaire	Covariate	Self-reported mental health treatment history (current/recent psychotherapy or psychiatric medication use)
Holmes Rahe Life Stress Survey (HRLSS)	Covariate	Self-reported exposure to moderate-to-major stressful life events
Prescribed Medication Questionnaire	Covariate	Self-report measure of currently prescribed medications, with a focus on psychiatric medications
Demographics Questionnaire	Covariate	Standard self-report measures of demographics (e.g., age, sex, ethnicity, education, etc.)
USDA Housing/Food Insecurity	Covariate	Self-report measure of household food security
Comorbidities Questionnaire	Covariate	Self-reported medical comorbidities commonly occurring with major depressive disorder
Trauma History Questionnaire	Covariate	Self-report measure of traumatic life events
Screening Assessment for Guiding Evaluation - Self-Report (SAGE-SR)	Covariate	An online, self-report-based comprehensive behavioral health diagnostic tool developed to cover the Diagnostic Statistical Manual (DSM); mirrors the Structured Clinical Interview for DSM Disorders.
TestMyBrain Neurocognitive battery (TMB)	Covariate	Computerized neurocognitive assessment; see Section 3.6
A/V recorded affect interview	Covariate	Seven-question affect induction interview; see Section 3.5.
Routines	Descriptive Measure	Self-report of daily activities and phone usage

Items listed as secondary outcome measures may also be utilized as covariates in some analyses. Full assessments and schedule of administration are available in the Supplementary material.

#### 3.2.3 Additional measures

In addition to primary and secondary outcome measures, participants will complete an array of assessments to obtain information about demographics and medical and psychiatric history. These will be used as covariates and sample descriptives, as well as potential outcome predictors in later analyses. These assessments are listed in Table 2 alongside descriptions of each metric.

### 3.3 Magnetic resonance imaging

All magnetic resonance imaging (MRI) data is obtained on a Siemens MAGNETOM Prisma 3 Tesla MRI scanner with a 32 channel head coil at the UCLA Staglin Center for Cognitive Neuroscience or the UCLA Ahmanson-Lovelace Brain Mapping Center. Prior to the MRI scan, all participants complete a comprehensive MRI safety screening to ensure their safety to undergo MRI. Participants are asked to remain still for the entire duration of the scan and are offered a short break halfway through the scan if needed. Participants recruited from the OPTIMA study receive their baseline MRI during week 13 of the OPTIMA protocol; the first LIFUP session typically is scheduled within 30 days of this scan. Participants who do not have MRIs from OPTIMA receive baseline scans 2–7 days prior to their first LIFUP session. All participants receive a second MRI scan 3–14 days after their third LIFUP session. All scans listed below are collected both at baseline and post-LIFUP, with the exception of the T2-weighted structural scan, which is only collected at baseline.

